### Outcome measurements

The primary outcome will be the incidence of PONV, which will be assessed at postoperative hours 4, 8, 16, 24, 32 and 48. A patient will be considered to suffer from PONV if nausea or vomiting is documented at any of the postoperative assessments.

One secondary outcome will be the severity of the PONV, measured with a score ranging from 0 to 3 (0 for no nausea; 1 for mild nausea, defined as nausea requiring a single administration of an antiemetic drug; 2 for severe nausea, defined as nausea requiring the repeated administration of antiemetic drugs; and 3 for nausea leading to vomiting).

Other secondary outcomes will be the intensity of pain at rest and under provocation (while rotating the neck 90° to each side), measured at postoperative hours 4, 8, 16, 24, 32 and 48 with a Verbal Rating Scale (VRS) ranging from 0 to 10, with 0 considered to be no pain and 10 considered to be the worst pain imaginable. Additional secondary outcomes will include the length of hospital stay (measured as the number of hours after the intervention), wound healing at the time of discharge and six weeks after the intervention, the amount of anesthetic medication required (total amount of administered fentanyl, remifentanil, rocuronium measured in mg and the total amount of administered remifentanil measured in μg) and postoperative in-hospital morbidity, including wound infection, reoperation, bleeding, prolonged intubation, laryngeal nerve lesion, urinary retention, urinary tract infection, pulmonary infection and gastrointestinal hemorrhage or newly occurring insulin dependence in diabetic patients.

For the safety analysis, adverse events (AEs) and serious adverse events (SAEs) will be evaluated. The patients will be instructed by the investigator to report the occurrence of any AE, defined as an unfavorable and unintended sign, symptom or disease temporally associated with the treatment provided in the present trial. The investigator (treating physician) will be asked to verify the absence or presence of all the AEs predefined on the CRF. Information in the patients’ medical files will be reported using the Common Terminology Criteria for Adverse Events v4.03 (CTCAE 4.03) coding system, rather than a narrative description. AEs will be scored as grade 1 (a mild AE) to grade 5 (death related to the AE), and a causality assessment will be performed.

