### Statistical analysis

The statistical analysis will be performed with SAS 9.1 (SAS Institute Inc., Cary, NC, USA). Missing values will be replaced with the last available value (the last observation carried forward approach, LOCF). For the baseline characteristics, descriptive statistics will be used as appropriate.

Two analyses (interims analysis and final analysis) will be performed for the primary outcome. To maintain the alpha, an O’Brien-Flemming alpha spending function [40] will be used. The alpha values used for the primary outcome will be 0.0039 in the interim analysis and 0.0488 in the final analysis. Both alphas will be adjusted for the exact proportion of information included in the interim analysis if the analysis is not performed for exactly 70 patients. For all other analyses, two-sided significance tests with an alpha of 0.05 will be applied.

All confirmatory analyses will be performed primarily as ITT analyses; the available data from all the patients will be assessed for the outcomes according to the randomization. To assess the treatment effects of dexamethasone vs. placebo in patients with no postoperative use of opioids, additional analyses will be conducted excluding the patients with protocol violations.

For the superiority analysis of dexamethasone vs. placebo in terms of the incidence of PONV (the primary outcome), a chi-square statistic will be applied. Mixed models assessing the mean ranks of the scores with adjustments for time and treatment vs. time interactions will be applied to analyze the following secondary outcomes: the severity of PONV, the intensity of pain at rest and the intensity of pain under provocation. The Mann–Whitney U statistic will be used to assess the following secondary outcomes: the required amount of anesthetic medication, the amount and type of postoperatively administered analgesics and the length of hospital stay. Postoperative morbidity and wound healing at the time of discharge and six weeks after the intervention will be assessed using a chi-square statistic.

Auxiliary, non-confirmatory analyses will be performed to assess the influences of baseline and treatment characteristics on the primary and secondary outcomes.

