We would like to acknowledge the potential limitations of this study protocol. First, although the scale for PONV measurement has been previously used it is not an explicitly validated scale. Nevertheless, as only patients vomiting or receiving antiemetic medication will be considered to suffer PONV the bias resulting from subjective ratings should be minimal. Second, recent studies suggested that 5-HT3 receptor antagonists might be more effective than dexamethasone in preventing postoperative nausea and vomiting [43]. Nevertheless, in times of constant pressure on health care expenses, the low cost and the general availability of dexamethasone still make it a relevant option for prevention of PONV. Third, although no opioids are applied in the postoperative course they are unavoidable during general anesthesia. Thus it could be possible that differences in operation time might lead to a different amount of applied remifentanil, potentially leading to a bias in PONV. As the study is randomized we consider such a bias very unlikely. However, since we record the amount of applied fentanyl and remifentanil, in case of an imbalance we will be able to adjust for this bias. Fourth, for pain measurement we will use a Verbal Rating Scale ranging from 0 to 10 instead of a 100 mm Visual Analog Scale. At our institution the use of this Verbal Rating Scale for pain measurement during the postoperative course is a common and well established clinical routine. Furthermore, patients are preoperatively informed to rate their pain using the Verbal Rating Scale.

In the present project, we reduced bias as much as possible. Thus, we expect to definitively clarify the efficacy of dexamethasone for PONV prophylaxis. The confirmation of this efficacy by our study will have a major impact because the results may establish dexamethasone administration before thyroidectomy as a new standard in clinical practice. Moreover, the results of this study could be applicable to all types of operations that involve general anesthesia and will stimulate further clinical research in this area.

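### The 0–3 PONV severity score has no level for nausea without an antiemetic and no clean level for vomiting without nausea, so a secondary outcome can misgrade patients whom the plan counts as PONV cases

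*Protocol article*

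**What the plan says.** All of the score's definition is in the Protocol article, Outcome measurements. The primary case definition there is broad: "A patient will be considered to suffer from PONV if nausea or vomiting is documented at any of the postoperative assessments". It does not require an antiemetic to have been given.

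The severity score follows directly. Its first three levels are "0 for no nausea; 1 for mild nausea, defined as nausea requiring a single administration of an antiemetic drug; 2 for severe nausea", where level 2 is tied to repeated antiemetic use; the top is "3 for nausea leading to vomiting".

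The Statistical analysis section analyses severity with mixed models on mean ranks, including time and treatment-by-time terms. It also sets a general rule for gaps in the data: "Missing values will be replaced with the last available value". It gives no rule for a patient who was assessed but whose state matches none of the four levels.

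The Discussion, commenting on this same scale, describes a narrower case: "as only patients vomiting or receiving antiemetic medication will be considered to suffer PONV the bias resulting from subjective ratings should be minimal". It concedes that the scale is not explicitly validated but does not mention uncovered states.

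**The concern.** An ordinal score analysed on ranks needs levels that are mutually exclusive, exhaustive and correctly ordered. Here the lowest step is the weak one. A nauseated patient who neither vomits nor receives an antiemetic cannot truthfully be scored 0, which means no nausea, and cannot be scored 1, which needs an antiemetic. That is the mildest form of the condition being graded. The rater must choose a level that is wrong, and the article does not say which.

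Two things are at stake. First, severity ranks for these patients depend on local habit rather than on a rule. Second, a reader would expect the proportion of patients who ever score above 0 to reproduce the primary PONV incidence. As written, it need not.

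The state is plausible. The Intervention/treatment section attaches a blood-pressure condition to the first-line antiemetic, so receipt of a drug is not determined by nausea alone.

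**Working it through.** **Step 1: map each possible state to the score and to the two case definitions.**

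| State at an assessment | Level as written | Case under Outcome measurements | Case under Discussion |
|---|---|---|---|
| No nausea, no vomiting, no antiemetic | 0 | no | no |
| Nausea, no vomiting, no antiemetic | none | yes | **no** |
| Nausea, no vomiting, one antiemetic administration | 1 | yes | yes |
| Nausea, no vomiting, repeated administration | 2 | yes | yes |
| Nausea leading to vomiting | 3 | yes | yes |
| Vomiting without reported nausea | 0 if read literally; 3 only by stretching | yes | yes |

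Two of the six states have no correct level. Reading the word requiring as need rather than receipt does not help, because nausea judged not to need a drug still has no level.

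**Step 2: compare the two case definitions.** They differ on one row, untreated nausea. Under Outcome measurements such a patient is a case without a valid grade. Under the Discussion the patient is not a case, but a score of 0 would still state falsely that there was no nausea. Vomiting without nausea is a case under both.

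**Step 3: expected numbers of cases.** The severity point disputes none of the plan's figures. As a check on the inputs, the plan's sample size reproduces. With 48% vs 24%, two-sided 0.05, power 0.80 and pooled variance, the fixed total is 123.2 (plan: 123). Then 123.2 × 1.006 = 123.9, i.e. 124, and 124 / 0.82 = 151.2, i.e. 152, or 76 per arm.

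- Placebo: 76 × 0.48 = 36.5 cases
- Dexamethasone: 76 × 0.24 = 18.2 cases
- Total: 54.7 cases

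**Step 4: illustration of size.** Let u be the share of cases whose only symptom is untreated nausea. The documents do not give u; 10% to 40%, equal in both arms, is an assumption.

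| | u = 0.10 | u = 0.40 |
|---|---|---|
| Cases without a valid score, placebo: 36.48 × u | 3.6 | 14.6 |
| Same, dexamethasone: 18.24 × u | 1.8 | 7.3 |
| Same, total: 54.72 × u | 5.5 | 21.9 |
| Share above 0 if these are scored 0, placebo: 0.48 × (1 − u) | 43.2% | 28.8% |
| Same, dexamethasone: 0.24 × (1 − u) | 21.6% | 14.4% |
| Difference (24 points before) | 21.6 points | 14.4 points |
| Ratio | 2:1 | 2:1 |

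The absolute difference shrinks and the score no longer agrees with the primary incidence. The ratio is unchanged, because u is taken as equal in the arms.

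**The case against.** The strongest defence is that the Discussion shows the intended scale to be treatment-based. Untreated nausea would then deliberately not be a case and would fall in level 0, so that a score above 0 would equal a PONV case after all. This has force as an explanation of intent. It does not settle the matter: the Discussion contradicts the definition in Outcome measurements, and it does not rewrite level 0, which still reads as no nausea.

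A second defence is that the score grades PONV and its top level is the vomiting level, so a rater would very likely enter 3 for any vomiting. That stands. The vomiting half is mostly a wording defect, and untreated nausea is the substantive half.

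Three stronger readings are tempting and are not supported:

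- *That LOCF will overwrite these records with an earlier grade.* LOCF applies to missing values. A patient who was assessed with nausea documented is not missing, and Setting and data collection locations describes drop-down entry with range and consistency checks. Carry-forward arises only if the field is left blank, and nothing in the article says it would be.
- *That the relative treatment effect is biased.* The illustration keeps the ratio at 2:1. A distortion of the relative effect would need different shares in the two arms, for example if dexamethasone moved patients from treated to untreated nausea. The documents offer no figure for this.
- *That the primary result is at risk from the score.* The primary chi-square test, the interim boundary and the sample size do not use it.

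An article may leave scoring instructions to the full protocol. Here, however, all four levels are stated with their definitions, so the fault lies in what is written rather than in what is left out.

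**Conclusion.** The point holds in limited form. The severity score as defined does not cover untreated nausea and covers vomiting without nausea only loosely, although both are PONV under the primary definition beside it. The rank analysis can misgrade such patients, chiefly those with untreated nausea, and the count scoring above 0 need not match the primary incidence.

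The size cannot be determined from the documents. The figure of about 5 to 22 of 55 expected cases rests on an assumed 10% to 40% share and on the planning incidences. The direction of any effect on the treatment comparison cannot be stated either, since it depends on how raters resolve the gap.

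The scoring gap itself is confined to a secondary outcome. The disagreement between Outcome measurements and the Discussion about what counts as a case is a separate contradiction, which also bears on the primary outcome and has to be resolved first. This is a change that should be made, not one on which the trial's main conclusion depends.

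**What to change.** 1. Reconcile Outcome measurements and the Discussion into one PONV case definition and use it throughout.
2. Make the score exhaustive and consistent with that definition: 0 for neither nausea nor vomiting; 3 for any vomiting, with or without reported nausea; and an explicit level for nausea without vomiting and without an antiemetic. That level can be pooled with level 1, or set as a separate lowest nausea level. Pooling hides a shift from one administration to none, so the separate level is needed if that shift is to be seen. The separate level is also needed if the narrower case definition is kept, because the cut-off for a case then lies above untreated nausea.
3. State which scores correspond to a PONV case, and let the CRF consistency check enforce it.
4. State that an observed record is never treated as missing, so LOCF cannot apply to it.
5. Trial status says recruitment is ongoing. Apply the rule before unblinding to every patient, including those already enrolled, by deriving the score from the recorded nausea, vomiting and antiemetic data.

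The change affects scoring only, not patient care. It costs a few lines in the outcome definition, one CRF rule and some rescoring. Step 5 assumes that the three inputs are recorded in a form that allows rescoring; the score already depends on them. The downside is a small departure from the previously used scale, and hence slightly less comparability with earlier work.

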## Background

### Scientific background and explanation of rationale

Postoperative nausea and vomiting (PONV) is a common and distressing problem that affects 20-30% of surgical patients after general anesthesia [1]. PONV not only reduces patient comfort but can also lead to serious postsurgical complications, such as dehydration, electrolyte imbalances, the aspiration of the gastric contents, esophageal rupture, suture dehiscence and bleeding [2-9]. Furthermore, PONV significantly affects healthcare costs by prolonging hospital stays [10,11]. In particular, patients undergoing thyroidectomy exhibit a high incidence of PONV, which can be as high as 80% [2,12,13]. PONV after thyroidectomy is most likely caused by edema and inflammation around the neck tissues, leading to evoked parasympathetic impulses through the vagus, recurrent laryngeal and glossopharyngeal nerves to the vomiting center [13-15].

Dexamethasone, a glucocorticosteroid, has been described as highly effective against chemotherapy-induced nausea and vomiting [16,17]. A recently published study comparing the efficacy of six well-established antiemetic strategies concluded that the use of dexamethasone as a first-line method of prophylaxis for PONV is a reasonable treatment option [18]. The exact mechanism by which dexamethasone exerts its antiemetic activity is not well understood. The antagonizing effect of corticosteroids on inflammatory reactions and the dexamethasone-triggered release of endorphins, which results in mood elevation, a sense of well-being and appetite stimulation, may contribute to this effect [19-21]. Due to their anti-inflammatory activity, corticosteroids have been shown to reduce postoperative swelling, pain and sore throat [22-25]. Despite these advantages, the perioperative use of dexamethasone for the prophylaxis and treatment of PONV has not been established [26], possibly due to concerns that the use of corticosteroids would increase susceptibility to infections. However, several studies have indicated that even long-term corticosteroids treatments do not lead to a significant increase in wound infections [27-29]. Another possible reason is the lack of awareness about the antiemetic effect of this type of medication.

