### Setting and data collection locations

The patients will be enrolled at the outpatient Clinic of Endocrine Surgery. The participants will be enrolled only by the head of the Clinic of Endocrine Surgery (TC) or under his direct supervision. For each randomized patient, a case report form (CRF) will be generated and updated continuously throughout the hospitalization period. CRFs specifically created for this trial will be used for documentation. All the CRFs are Microsoft Excel-based, and the data will be entered electronically. The CRFs contain extensive probability and range checks to reduce erroneous entries, they are designed to reduce free-text entries to the minimum necessary, and selection from predefined lists (drop-down menus) will be the preferred means of data entry. The completed forms will be printed and signed by the entering physician and then sent to the trial coordinator, along with the data files. The six-week follow-up visits will occur at the outpatient Clinic of Endocrine Surgery.

Several procedures have been designed to enhance the quality of the trial conduct: reviews of the protocol and forms, the direct entry of the data into Excel data entry forms whenever possible, the automatic performance of consistency checks by the electronic data forms, the entry of written or printed data into electronic forms and a review of the data by the trial chair or a delegated person (with the medical content of all the forms reviewed and approved by a monitor).

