All grade 4 or 5 AEs will be counted as SAEs, with the exclusion of PONV (as the primary outcome), delayed wound healing (as a secondary outcome) and wound infection (as a secondary outcome). Additionally, postoperative hypoparathyroidism and lesions to the recurrent nerve will not be counted as SAEs because they are considered imminent risks of a thyroidectomy.

The local Ethics Committee and Swissmedic will be informed by the principal investigator about SAEs according to local legislation (VKlin/HMG). A yearly safety summary will be provided to the local Ethics Committee and Swissmedic.

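### A wound infection after discharge is neither a secondary-outcome event nor, even at grade 4 or 5, an SAE, although a six-week visit is planned

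*Protocol article*

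**What the plan says.** All references are to the protocol article.

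- **Outcome, in hospital.** Outcome measurements lists among the secondary outcomes "postoperative in-hospital morbidity, including wound infection".
- **Outcome, later.** The only secondary outcome that this section places at week 6 is "wound healing at the time of discharge and six weeks after the intervention". Setting and data collection locations confirms the visit: "The six-week follow-up visits will occur at the outpatient Clinic of Endocrine Surgery".
- **AEs.** Outcome measurements states "The patients will be instructed by the investigator to report the occurrence of any AE". AEs are graded 1 to 5, assessed for causality, and evaluated alongside SAEs in the safety analysis. No end date for AE collection is given.
- **SAEs.** The rule is "All grade 4 or 5 AEs will be counted as SAEs". Among the listed exceptions are "delayed wound healing (as a secondary outcome) and wound infection (as a secondary outcome"). No grade limit is attached to the exception.
- **What depends on SAE status.** Outcome measurements ties notification of the Ethics Committee and Swissmedic to SAEs. Interim analysis describes the safety tables as tables of SAEs.
- **Analysis.** Statistical analysis puts morbidity and wound healing into one sentence, with discharge and six weeks as time points and a chi-square test. It does not repeat the in-hospital limit.
- **Rationale.** The Background gives, as a possible reason why perioperative dexamethasone is not established, "concerns that the use of corticosteroids would increase susceptibility to infections".

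**The concern.** An event is normally kept out of the SAE count on the ground that it is already captured, by arm, as an outcome. Here the two windows do not match. The outcome closes at discharge, while the SAE exemption has no end. For the weeks between discharge and the six-week visit, the exemption has lost the only reason given for it.

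The affected event is the harm that the Background itself links to corticosteroids, and morbidity and wound healing are both in the stated aim. If the wound-infection comparison stops at discharge, a finding of no difference between arms speaks only to the hospital stay. A severe infection that appears later would not enter the SAE reports to the authorities or the safety tables seen at the interim analysis.

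**Working it through.** The plan states no figure for wound infection, so there is nothing to reproduce. The check is to follow a wound infection along each route that the document describes.

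| Route | Infection in hospital | Infection from discharge to week 6 |
|---|---|---|
| Morbidity outcome (Outcome measurements) | Counted | Not counted: the outcome is limited to the hospital stay |
| SAE (Outcome measurements) | Exempt at every grade | Exempt at every grade |
| Notification of authorities, linked to SAEs (Outcome measurements) | Not reached | Not reached |
| SAE tables (Interim analysis) | Not reached | Not reached |
| AE in the safety analysis (Outcome measurements) | Counted | Counted in principle; no window stated |
| Wound healing (Outcome measurements) | May show at discharge | May show at week 6; infection not named |

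Four steps follow.

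1. **The stated reason expires.** The exemption reads "wound infection (as a secondary outcome"). In the left column that is true. In the right column it is not, because the first row is empty there.
2. **The exemption reaches the top of the scale.** SAEs are grade 4 or 5 by definition, and grade 5 is death related to the AE. With no grade limit, the exemption removes every wound infection that could have become an SAE. (The interim tables are described as covering SAEs of grades 3 and 4, so on that wording the exemption affects them through grade 4.)
3. **Wound healing is not a substitute on the text.** The SAE exceptions name delayed wound healing and wound infection as two items. An infection that was treated and had healed before the visit need not show in a healing assessment at week 6.
4. **The analysis sentence does not settle the window.** If its two time points apply to wound healing only, morbidity remains in-hospital and the gap stands. If they apply to morbidity as well, Statistical analysis contradicts the in-hospital limit in Outcome measurements. Either reading requires an edit.

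**The case against.** The strongest reply is that such an infection is still recorded. Patients are told to report any AE, every AE is graded and evaluated for safety, and the exemption removes wound infection from the SAEs, not from the AEs. This stands. A reader might infer that a late wound infection is counted nowhere; the document does not support that. What remains is that the AE route has no stated window, and that the CRF is described as being updated through the hospitalization period. Capture after discharge is therefore possible but not secured.

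A second reply is that the six-week wound assessment may record infection, and that the CRF and full protocol are not shown. That is fair as to what the form contains. It does not repair the mismatch between a stated outcome window and a stated exemption, which are both in the article.

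A third reply is that infection is not called the main safety question anywhere. The Background offers it only as a possible explanation for low use, and then cites studies without a significant increase in wound infections. This also stands, and the point does not rest on it.

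Finally, the trial is small for this harm. Even with full capture and no event among the 76 patients of one arm, the one-sided 95% upper limit is 1 − 0.05^(1/76) = 3.9%. Better counting would make the comparison honest about its window; it would not make it decisive.

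**Conclusion.** The inconsistency is real and should be corrected. As written, a wound infection after discharge falls outside the secondary outcome and outside the SAEs at any grade, and at grade 4 or 5 it also misses the reporting that depends on SAE status. It is left to AE reporting without a stated window and to a wound-healing assessment that does not name infection.

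The size cannot be expressed as a number. The document gives no wound-infection rate, no length of stay and no split of infections before and after discharge, so any statement about the share of events missed would be assumption alone. The conclusion rests on reading the in-hospital qualifier in Outcome measurements as applying to wound infection, which is what the sentence says. If the sponsor intended the six-week reading of the Statistical analysis sentence, the outcome gap closes, but the two sections contradict each other and the SAE exemption still has no upper grade.

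**What to change.** 1. In Outcome measurements, define the wound-infection outcome as any wound infection from surgery to the six-week visit, compared by arm, and report the in-hospital count as a subset.
2. In the SAE definition, remove wound infection from the list of exceptions, so that infections of grade 4 or 5 enter the SAE reports and the interim safety tables.
3. Reconcile Outcome measurements and Statistical analysis, so that the window for morbidity, and for wound infection within it, is the same in both.

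The cost is small. The six-week visit already takes place, so the change needs one more field there and brings a few more events to report. Trial status says that recruitment is ongoing, so the wording should be changed by amendment before the treatment comparison is seen. For patients already past week 6, the amendment should say how the item will be completed, or that it is missing.

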## Methods/design

The study was planned according to the updated Consolidated Standards of Reporting Trials (CONSORT) statement [36] and according to the Declaration of Helsinki, the Guidelines of Good Clinical Practice issued by ICH and the requirements of Swiss regulatory authorities.

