### Interim analysis

An interim analysis is planned to assess the primary outcome and the safety of the treatment after 70 patients. For the interim analysis, the data manager will provide the data to the trial statistician with coded treatment assignments (A, B). The statistician will provide summary tables of grade 3 and 4 SAEs and a blind analysis of the primary outcome. Based on these data, the trial chairperson and co-chairperson will decide whether to continue the trial without modifications, continue the trial with modifications or halt the trial due to safety or efficacy concerns. Only if the results are insufficient for that decision the treatment assignments will be revealed and the data will be analyzed again. Unless the benefit of the treatment is demonstrated “beyond a reasonable doubt” by the interim analysis, no formal discontinuation due to efficacy is foreseen. The decision about trial continuation will be based not only on the statistical results but also on clinical judgment [41]. The statistical boundary, requiring p < 0.0039 at the interim analysis to halt due to efficacy, will serve as a guide. The results of the interim analysis will be confidential and strictly limited to the trial statistician, trial chairperson and trial co-chairperson. To avoid bias in the subsequent trial, the results of the interim analysis will be treated confidentially and will not be communicated to the outside or to the clinical investigators involved in the trial.

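### The only SAE criterion stated is a severity grade (CTCAE 4 or 5), and it conflicts with the interim safety table, which is planned for SAEs of grade 3 and 4

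*Protocol article*

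**What the plan says.** Under Outcome measurements, adverse events are graded by CTCAE 4.03: "AEs will be scored as grade 1 (a mild AE) to grade 5 (death related to the AE), and a causality assessment will be performed". The rule for SAEs follows: "All grade 4 or 5 AEs will be counted as SAEs". Three study outcomes are taken out of this rule by name: PONV, delayed wound healing and wound infection. A further sentence says that "postoperative hypoparathyroidism and lesions to the recurrent nerve will not be counted as SAEs". No other criterion for an SAE is printed in the article.

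On reporting, the same section says: "The local Ethics Committee and Swissmedic will be informed by the principal investigator about SAEs according to local legislation". A yearly safety summary also goes to both bodies, with its content not described.

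Under Interim analysis, the safety material for the single interim look, after 70 patients, is described as follows: "The statistician will provide summary tables of grade 3 and 4 SAEs and a blind analysis of the primary outcome". The chairperson and co-chairperson use these data to decide whether to continue, modify or halt the trial.

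Under Methods/design, the trial is said to be planned according to "the Guidelines of Good Clinical Practice issued by ICH", among other standards.

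**The concern.** Severity and seriousness are different properties of an adverse event. A CTCAE grade describes how intense the event is. Seriousness describes what it led to, such as a threat to life, a longer hospital stay or lasting harm. A rule built on grade alone can leave out an event of moderate grade with important consequences for the patient.

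This matters because the article attaches two functions to SAE status: notification of the Ethics Committee and Swissmedic, and the safety tables for the interim decision. If the definition and the table use different grades, the people preparing the table cannot tell which events belong in it. The interim look is the one planned point at which the trial can be halted for safety on accumulated data, so its safety input should be unambiguous.

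**Working it through.** No arithmetic applies: the article gives no adverse event rates, and the point depends on no sample size, power or alpha. The check is to set the sections side by side.

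**Step 1. Which grades does each section treat as SAEs?** The table leaves aside the named exclusions.

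| CTCAE grade | SAE by the rule in Outcome measurements | Named for the SAE table in Interim analysis |
|---|---|---|
| 1-2 | not stated | no |
| 3 | not stated | yes |
| 4 | yes | yes |
| 5 | yes | no |

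The definition covers {4, 5} and the table covers {3, 4}; the overlap is {4}. If the definition is complete, the grade 3 part of the table is empty by construction. If the table is right that grade 3 SAEs exist, the definition is incomplete and the criterion for those events is not given. In either case a grade 5 event, which the article describes as a death related to the adverse event, is an SAE that the table does not name.

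**Step 2. Is there any other criterion for seriousness?** The article was searched for a rule based on hospitalisation, prolonged stay, disability or medical importance. There is none. The ICH guidelines are named, but their definition is not reproduced or linked to the SAE rule.

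**Step 3. What happens to a grade 3 event with serious consequences?** Take a reoperation, a bleed, or a hospital stay prolonged by an adverse event, graded 3.
- SAE status: no stated route under Outcome measurements.
- Notification: tied to SAEs and to local legislation, whose definition is not shown.
- Interim table: grade 3 SAEs are named, but the event is not an SAE under the only printed rule. Its inclusion is therefore contradictory.
- Final analysis: reoperation, bleeding and length of stay are secondary outcomes and are compared between arms (Statistical analysis). The event is recorded.
- Interim decision: the listed inputs are the SAE tables and the primary outcome. In-hospital morbidity and length of stay are not listed, so their collection does not by itself bring the event to the interim review.

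**Step 4. What do the named exclusions do?** PONV, delayed wound healing, wound infection, hypoparathyroidism and recurrent nerve lesions are taken out by name, not by grade. A wound infection is therefore outside the SAE count even at grade 4 or 5. The Background gives concern about infection as a possible reason why perioperative dexamethasone is not established. Changing the grade threshold alone would not alter this, so the exclusions need their own statement.

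**The case against.** The strongest reply is that the rule says all events of grade 4 or 5 count, not that only these count. It can be read as an automatic trigger beside an unprinted definition, and the mention of grade 3 SAEs at the interim suggests that the authors had a wider definition in mind. Notification follows local legislation, which may carry its own definition. The article also commits to ICH guidance and Swiss requirements, and a journal article may leave the full SAE definition to the full protocol.

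Much of this stands, and it limits what can be claimed. A reader might infer that a grade 3 reoperation can never be an SAE and reaches neither the authorities nor the interim table. The documents do not support that: the interim table expressly names grade 3, the legislation is not shown, and the content of the yearly summary is not stated. Nor are such events lost, since all adverse events are graded and evaluated and the main complications are secondary outcomes. A reader might also want a count of missing SAEs. None can be given, because the article has no event rates and no distribution of grades.

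The reply does not remove the conflict. The article does more than omit a definition: it prints a counting rule with its own list of exceptions, which is how an operative rule reads, and a second section uses a different set of grades. If a wider definition exists elsewhere, the printed rule and the printed table still disagree on grades 3 and 5.

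**Conclusion.** The point holds in a limited form. The only printed SAE criterion is a severity grade, with no criterion based on outcome, and it contradicts the planned interim table on grades 3 and 5. As written, a serious event of grade 3 has no stated SAE route, and its place in the interim safety review is contradictory rather than excluded.

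The consequences are confined to the SAE count, SAE notification and the safety input to the interim decision. The primary outcome, the sample size and the alpha levels are untouched. The number of affected patients is unknown. The finding about grades rests on the text alone. The practical consequence assumes that staff apply the rule as printed; a fuller definition in documents not shown, or in the legislation, would reduce it. The change is worth making because it is cheap and concerns safety review.

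**What to change.** Reconcile the two sections with one definition:

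1. In Outcome measurements, define SAE status by seriousness criteria that do not depend on grade, consistent with the trial's commitment to ICH Good Clinical Practice. Keep the CTCAE grade as a separate severity field.
2. State whether each named exclusion still applies under the new definition and, if so, where those events are reviewed instead. This matters most for wound infection.
3. In Interim analysis, have the table show all SAEs, including grade 5, together with all adverse events of grade 3 or higher, by coded arm (A, B). The existing blinding arrangement is kept.

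The cost is amended wording in two sections and one added field on the CRF. The downside is a few more SAE forms in a trial of 152 patients. For patients already enrolled (the article reports that recruitment is ongoing), recorded adverse events would need to be reclassified once under the new definition so that the count is consistent over the trial.
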